### Sample size calculation

Based on data from the literature [24], using the EMG signal of the masseter muscles, and following LLLT as the basis, with mean values of 13.4 (standard deviation: 2.8) and 11.9 (standard deviation: 1.9) individuals per group, for the experimental study and comparison of means with equal samples (hypothesis test), considering a 5% level of significance (*P* < 0.05) and 80% test power, the sample size was determined to be 15 individuals per group, using the DINAM 1.0 program [32].

Seventeen individuals will be selected for each group to compensate for possible losses.

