#### Organization and statistical treatment of data

The data will be tabulated and treated using the SPSS 12.0 program for Windows and will be submitted to descriptive statistical analysis. The chi-square test and Fisher’s exact test will be used to determine associations among the categorical variables. The Student’s *t* test for paired data will be used to analyze the averages of electromyographic and occlusal contacts before and after treatment. The Student’s *t* test and analysis of variance will be used to compare mean electromyographic signals and occlusal contacts between different groups. For data that are not normally distributed, the differences before and after treatment in the same group and between groups will also be analyzed, using the Mann–Whitney and Wilcoxon paired tests. Pearson’s correlation coefficients will be calculated for the analysis of correlations among the continuous variables. The level of significance will be set to 5% (*P* < 0.05).

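### The sample size of 15 per group does not follow from its stated inputs: a two-sided comparison of two independent groups needs about 41, and 15 to 17 per group gives about 38–43% power, not 80%

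*Protocol article*

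**What the plan says.** The Sample size calculation section of the protocol article rests on one outcome, "using the EMG signal of the masseter muscles, and following LLLT as the basis", with figures from a cited study: "with mean values of 13.4 (standard deviation: 2.8) and 11.9 (standard deviation: 1.9) individuals per group". (The word individuals appears misplaced there; 13.4 and 11.9 are evidently EMG values.) The method is described as "comparison of means with equal samples (hypothesis test"), "considering a 5% level of significance" and 80% power. The result is that "the sample size was determined to be 15 individuals per group". The section then adds: "Seventeen individuals will be selected for each group to compensate for possible losses". Five groups of 17 make the 85 participants named in the Abstract.

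The section does not say whether the test is one- or two-sided. It gives no within-subject correlation and no SD of change.

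For the analysis, the section on organization and statistical treatment of data plans a paired t test of EMG before and after treatment. For comparisons between groups it says that the Student's t "test and analysis of variance will be used to compare mean electromyographic signals and occlusal contacts between different groups".

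**The concern.** The section supplies everything a two-sample calculation needs: two means, two SDs, a significance level, a power and equal group sizes. A standardised difference near 0.6 normally calls for about 40 per group, so 15 looks far too small.

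This is the only power statement in the document, and the total of 85 rests on it. The trial is randomised and placebo-controlled, so the comparisons that justify the design are between each laser group and placebo. If 80% power is not supported for them, a reader who relies on that figure could take a non-significant result as evidence that the laser does not change masseter EMG, when the trial had well under the stated chance of detecting the planned difference.

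**Working it through.** **Inputs (Sample size calculation section).** Means 13.4 and 11.9; SDs 2.8 and 1.9; 5% level; 80% power; equal groups; stated n = 15, enrolled n = 17. Sidedness is not stated; two-sided is taken as the default, and one-sided is also tried.

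**Step 1: standardised difference.**
- Difference = 13.4 − 11.9 = 1.5
- Pooled SD = √((2.8² + 1.9²)/2) = √((7.84 + 3.61)/2) = √5.725 = 2.393
- d = 1.5/2.393 = 0.627

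**Step 2: attempt to reproduce 15 with two independent groups.**
- Normal approximation, two-sided: n = 2 × (1.96 + 0.8416)² × 5.725/1.5² = 39.9, so 40 per group.
- Exact (noncentral t), two-sided: 40.9, so 41 per group.

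The stated 15 is not reproduced. Other two-sample choices, by exact t:

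| SD used | Two-sided n per group | One-sided n per group |
|---|---|---|
| Pooled, 2.393 | 41 | 33 |
| Larger SD, 2.8, in both groups | 56 | 44 |
| Smaller SD, 1.9, in both groups | 27 | 21 |

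Even the most favourable cell, which ignores the larger SD and tests one-sided, needs 21. A one-way ANOVA over four or five groups needs about 27 to 62 per group, depending on the assumed pattern of means.

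**Step 3: power at the planned sizes (difference 1.5, pooled SD).**

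| n per group | Two-sided t | One-sided t | Stated |
|---|---|---|---|
| 15 | 38.1% | 51.2% | 80% |
| 17 (no losses) | 42.6% | 55.7% | – |

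Simulation that keeps the SDs unequal gives almost the same two-sided power: Student 38.3% and 42.8%, Welch 37.8% and 42.3%. With 41 per group the simulated power is 80%.

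**Step 4: what 15 per group can detect.** For two-sided 80% power, the detectable standardised difference is 1.060 at n = 15 and 0.991 at n = 17. In EMG units this is 1.060 × 2.393 = 2.54 and 0.991 × 2.393 = 2.37, against the planned 1.5. Put another way, 15 per group would suffice for 1.5 only if the common SD were about 1.42 (1.5/1.060), which is below both quoted SDs.

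**Step 5: could a paired calculation give 15?** For a correlation r between the before and after values, SD of change = √(2.8² + 1.9² − 2r × 2.8 × 1.9). The values of r are assumptions, since the protocol gives none.

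| Assumed r | SD of change | n, two-sided paired t | n, one-sided paired t |
|---|---|---|---|
| 0.5 | 2.48 | 23.4 | 18.3 |
| 0.6 | 2.25 | 19.7 | 15.4 |
| 0.7 | 2.00 | 16.0 | 12.5 |
| 0.73 | 1.92 | 14.9 | 11.6 |
| 0.8 | 1.71 | 12.3 | 9.6 |

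So 15 is reached at r of about 0.73 two-sided, or about 0.61 one-sided.

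**The case against.** The strongest reply is that a paired calculation was meant. The two means come from a cited study of laser treatment and are never labelled as two arms, so they could be before and after values. The analysis section also lists the paired EMG test ahead of the between-group tests. The cited study and the software output are not available here, so this reading cannot be excluded.

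It does not rescue the paragraph. The description as a comparison of means with equal samples, with figures per group, points to two groups. A paired calculation also needs a correlation or an SD of change, and without one a reader cannot obtain 15. Above all, it would size only change within one group, leaving the planned comparisons between groups without any sample size basis.

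A second reply is that 38–43% describes one analysis only, a comparison of single values between groups. A t test on before-to-after changes could do better or worse. For a 1.5-unit difference in change, using the SD of change from Step 5 in both groups, power is 36% at n = 15 and 40% at n = 17 if r = 0.5, and 54% and 60% if r = 0.73. This point stands as a qualification, but none of these figures reaches 80%.

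A third reply is that sidedness is unstated. That also stands: with a one-sided test, power is just above one half, so only under a two-sided test would the trial miss the planned difference more often than it finds it. The required number would still be 33, not 15.

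**Conclusion.** The concern holds. As a two-sided comparison of two independent groups, which is the natural reading of the text, the stated inputs require 41 per group, about 2.7 times the stated 15. Power for the planned 1.5-unit difference is about 38% with 15 evaluable per group and 43% if all 17 are retained. No two-sample variant tried comes closer to 15 than 21.

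These figures assume normal outcomes, the quoted means and SDs, and a single contrast at the full 5% level. If the three laser–placebo contrasts were tested with a Bonferroni correction, which the protocol does not plan, two-sided power would be about 22% and 26%. The exact percentages depend on sidedness and on whether single values or changes are compared. The conclusion that 80% power is unsupported for a between-group comparison does not.

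**What to change.** Enrolment can stay as planned; the statement should be corrected. Either of these would do:

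- **Restate the power or the target.** For a two-sided 5% comparison of two groups with SDs 2.8 and 1.9, 15 evaluable per group gives about 38% power for a difference of 1.5 (about 43% with 17). Alternatively, state that 80% power applies to a difference of about 2.5 units (standardised difference about 1.06) with 15 per group.
- **Disclose a paired basis, if that was the intention.** Name the test and its sidedness, give the correlation or SD of change and its source, and say that the calculation does not size the comparison with placebo.

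In both cases, commit to reporting between-group EMG differences with confidence intervals, and state that a non-significant result will not be read as no effect.

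The cost is one corrected paragraph and a less favourable power figure, with no additional participants. By comparison, keeping 80% power for 1.5 units would take 4 × 41 = 164 evaluable participants in the four TMD groups alone, or 5 × 41 = 205 across all five groups.

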#### Organization and statistical treatment of data

The data will be tabulated and treated using the SPSS 12.0 program for Windows and will be submitted to descriptive statistical analysis. The chi-square test and Fisher’s exact test will be used to determine associations among the categorical variables. The Student’s *t* test for paired data will be used to analyze the averages of electromyographic and occlusal contacts before and after treatment. The Student’s *t* test and analysis of variance will be used to compare mean electromyographic signals and occlusal contacts between different groups. For data that are not normally distributed, the differences before and after treatment in the same group and between groups will also be analyzed, using the Mann–Whitney and Wilcoxon paired tests. Pearson’s correlation coefficients will be calculated for the analysis of correlations among the continuous variables. The level of significance will be set to 5% (*P* < 0.05).

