#### Surface electromyography

The EMG signal will be determined using a four-channel acquisition system (*EMG System do Brasil Ltda*) made up of a signal conditioning module, active bipolar electrodes with 20× pre-amplification, analog band-pass filter (20 to 500 Hz) and 120 dB common rejection mode. The sampling frequency will be 2 kHz. The signal will be digitized using an analog-to-digital converter with 16-bit resolution. The acquisition program will be EMGLab (*EMG System do Brasil Ltda*).

To capture the EMG of the right and left masseter and anterior temporal muscles, the skin will be cleaned with alcohol to diminish impedance and disposable, self-adhesive anterior surface electrodes (Ag/AgCl, Meditrace) measuring 10 mm in diameter will be attached to the belly of the muscle in the region with the greatest tone after the volunteer performs moderate intercuspation. The interelectrode distance will be 20 mm from center to center, as suggested by the European Recommendations for Surface Electromyography [27]. An electrode placed on the left wrist of the volunteer will be used as reference to impede the interference of external noise.

The EMG activity of the masseter and anterior temporal muscles will be read under three conditions: (i) at rest; (ii) during chewing (isotonic); and (iii) during maximum intercuspation (MI) (isometric). The signals referring to the resting and chewing conditions will be measured with no material placed between the upper and lower arches. During the readings, the volunteer will remain seated comfortably in a chair with hands resting on the thighs. Three readings will be made under each condition, with a three-minute rest interval between readings. The readings in the resting position will be taken first and each reading will last 15 seconds. The readings for the chewing condition will be taken next, with the volunteer simulating habitual chewing at a pace determined by a metronome adjusted to 60 beats a minute; each reading will last 15 seconds. The MI readings will then be performed. Three 10-second readings will be performed with no material placed between the arches, followed by three 5-second readings during maximum clenching effort (MCE) with a folded layer of Parafilm M® [28], 3 mm thick (15 mm × 35 mm) between the molars (bilaterally).

The EMG will be carried out before and after LLLT treatment.

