#### Application of low-level laser therapy

A gallium-aluminum-arsenide laser (Twin Flex Evolution®, MM Optics) will be employed for the LLLT and placebo treatment. The sessions will be held in a reserved, noise-free room. The volunteer will be positioned with the Frankfurt plane parallel to the ground. The active tip of the laser will be covered in disposable plastic wrap to avoid cross-contamination and for hygiene reasons. The operator will wear suitable protective clothing. The skin at the site to be irradiated will have previously been cleaned with 70% alcohol. Both the operator and volunteer will use protective eyewear.

Two sessions of LLLT or placebo treatment will be carried out over six weeks (a total of 12 sessions). The device will be calibrated with a wavelength of 780 nm, an energy density of 25 J/cm^2^, a power of 50 mW, and a power density of 1.25 W/cm^2^. The exposure time will be 20 s per point, resulting in a total energy of 1 J per point. The spot application method will be used: the laser will have a conventional tip in contact with the skin and will cover an area of 0.04 cm^2^, as suggested by Venezian *et al*. [24] and Carvalho *et al*. [14]. Three of the four groups with TMD will receive LLLT and one will receive a placebo treatment:

1. TMJ region: five points around the TMJ [7,13], totaling 5 J.

2. Masseter and temporal muscles: three points on the masseter (upper, middle and lower) and one point on the anterior temporal [24], totaling 4 J.

3. Mixed application: TMJ and muscles of mastication [12,14], resulting in 9 J.

4. Placebo treatment: the same equipment will be used with a pen that emits a red guide light and a warning sound, but without the emission of a laser beam.

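### The plan does not say which test decides efficacy, names no laser-versus-placebo contrast, and leaves baseline out of its parametric between-group analysis

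*Protocol article*

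**What the plan says.** All references are to the protocol article.

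- **Within groups** (Organization and statistical treatment of data): a "test for paired data will be used to analyze the averages of electromyographic and occlusal contacts before and after treatment".
- **Between groups** (same section): the t test and "analysis of variance will be used to compare mean electromyographic signals and occlusal contacts between different groups". No baseline covariate, change score or group-by-time term is attached to this analysis, and no pair of groups is singled out.
- **Non-normal data** (same section): Mann–Whitney and Wilcoxon tests are named, and "the differences before and after treatment in the same group and between groups will also be analyzed".
- **Arms** (Application of low-level laser therapy): "Three of the four groups with TMD will receive LLLT and one will receive a placebo treatment". Table 1 adds Group I, in which the disorder is absent and which is labelled the control group.
- **Baseline data**: the section on surface electromyography says "The EMG will be carried out before and after LLLT treatment". Occlusal contacts are recorded at the start and end of treatment and again 30 days after the last session.
- **Planning figures** (Sample size calculation): "mean values of 13.4 (standard deviation: 2.8) and 11.9 (standard deviation: 1.9) individuals per group", for a "comparison of means with equal samples (hypothesis test"), with 80% power, giving 15 per group, raised to 17 for losses.

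**The concern.** The trial randomises participants with the disorder to three laser arms and a placebo arm. The inference this design supports is each laser arm against placebo. The plan lists two families of tests and does not say which one answers the efficacy question.

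The two are not interchangeable. A before/after change within an arm mixes any laser effect with natural course, regression to the mean and repeated testing, all of which also act in the placebo arm. A significant change under laser beside a non-significant change under placebo is not a test of the difference between them.

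The between-group family is the right kind of analysis but is loosely aimed. An analysis of variance across all groups could be significant only because Group I does not have the disorder. The parametric version also leaves aside a baseline value that is planned for both outcomes, and so gives up precision in small groups.

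**Working it through.** **Inputs from the protocol.** Means 13.4 and 11.9, SDs 2.8 and 1.9, 5% significance, 15 per group. Sidedness is not stated; two-sided is assumed. The before/after correlation r and any change shared by all arms are not given, so ranges are used.

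**1. The plan's own figure.** Difference = 13.4 − 11.9 = 1.5. Pooled SD = √[(2.8² + 1.9²)/2] = √5.725 = 2.393. Standardised difference d = 1.5/2.393 = 0.627. A two-sided two-sample comparison at 80% power needs 40 per group by the normal approximation and 41 by the t distribution. The stated 15 is not reproduced. That is a separate sample-size matter; here the inputs serve only to compare analyses.

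**2. Precision of the between-group test.** Power comes from the noncentral t distribution with 2n − 2 degrees of freedom and noncentrality d√(n/2). ANCOVA multiplies the residual variance by 1 − r², so d becomes d/√(1 − r²). (Spending one degree of freedom on the covariate changes power by about 0.1 percentage point.)

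| Analysis, n = 15 per group | 1 − r² | Effective d | Power |
|---|---|---|---|
| Unadjusted means | 1 | 0.627 | 38% |
| ANCOVA, r = 0.3 | 0.91 | 0.657 | 41% |
| ANCOVA, r = 0.5 | 0.75 | 0.724 | 48% |
| ANCOVA, r = 0.7 | 0.51 | 0.878 | 64% |

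The normal approximation gives slightly higher values (40%, 44%, 51% and 67%) and the same pattern.

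**3. What happens if within-group results are read as efficacy.** Suppose laser adds nothing to placebo and all four randomised arms share the same true standardised change. Let p be the power of the paired t test in one arm of 15, and q = 1 − p. With independent arms, the chance that at least one of three active arms is significant while placebo is not is q(1 − q³).

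| Shared standardised change | p | q(1 − q³) |
|---|---|---|
| 0 | 0.050 | 0.950 × (1 − 0.857) = 14% |
| 0.3 | 0.192 | 0.808 × (1 − 0.528) = 38% |
| 0.5 | 0.438 | 0.562 × (1 − 0.178) = 46% |
| 0.7 | 0.713 | 0.287 × (1 − 0.024) = 28% |

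The 14% with no change comes from having three active arms, since 1 − 0.95³ = 14.3%. The rise above it comes from the shared change. The expression q − q⁴ cannot exceed about 47%, so the value at 0.5 is close to the worst case. It falls again for larger changes because placebo then becomes significant too.

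**The case against.** - **Ranking of the tests.** A reader might infer that the trial judges efficacy by the within-group tests, and so will produce false claims for laser. The text does not support that. The paired tests come first, but the between-group tests follow in the next sentence and neither is ranked above the other. The percentages in the second table need a rule (active arm significant, placebo not, therefore laser works) that the protocol never states. This objection stands: the fault is that the decisive test is left open, not that the wrong one was chosen.
- **Validity of the planned comparison.** Comparing unadjusted end-of-treatment means between randomised arms is unbiased and keeps its type I error per test. This also stands. The loss is of precision only, and its size depends on a correlation the document does not give; near zero there is almost no gain.
- **Baseline may already be used.** The sentence on non-normal data can be read as comparing before/after differences between groups. A flat statement that the plan ignores baseline would therefore be too strong. But that sentence is ambiguous and tied to non-normal data, and it does not alter the parametric analysis. On change scores the residual variance factor would be 2(1 − r), which is 0.60 at r = 0.7 against 0.51 for ANCOVA, and 1.00 at r = 0.5 against 0.75.
- **Condensed article.** Covariates and primary contrasts are often left to a fuller document. That would excuse silence. Here the article states the tests, and as stated they do not separate the randomised comparison from the rest.

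**Conclusion.** The point holds in a limited form. The statistical section lists within-group paired tests and an unadjusted comparison of group means. It does not say which decides efficacy, names no active-versus-placebo contrast, and does not exclude the non-randomised Group I.

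For precision, at 15 per group and with the protocol's planning figures, baseline adjustment would raise two-sided power by about 3, 10 or 26 percentage points from 38%, for an assumed correlation of 0.3, 0.5 or 0.7.

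The risk of misreading is conditional. Only if within-group results were taken as evidence of efficacy would a null trial give the misleading pattern in about 14% of cases with no shared change, or 28–46% with a shared standardised change of 0.3–0.7. These figures assume independent arms of 15 and equal true change in every arm. They are not the error rate of the planned between-group test.

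**What to change.** In the statistical section:

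1. Name the efficacy analysis: an ANCOVA of the end-of-treatment value on randomised group (II–V), with the baseline value of the same outcome as covariate.
2. Report each of the three active-minus-placebo differences with its 95% CI, and repeat this at 30 days for outcomes measured then (occlusal contacts; no 30-day electromyography is planned).
3. Label the within-group paired tests, and any comparison with Group I, as descriptive, with no efficacy claim drawn from them.
4. Reword the sentence on non-normal data so that it is clear whether changes or end values are compared between groups.

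The cost is wording only: the measurements are already planned, and the article reports that recruitment is still under way. The change does not by itself deliver the stated 80% power: even at r = 0.7, power at 15 per group is 64%. The sample-size calculation needs its own correction.

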Low-level laser therapy (LLLT) is a low-cost noninvasive treatment that has proven to be beneficial in the treatment of pain related to TMD [1-3,6,11,19-22]. The therapeutic effects of LLLT include the modulation of inflammatory processes, analgesia and cellular activity [1-3,6,7,11-13,19-25]. Despite the reported benefits [1-3,6,11,20-22], few studies have analyzed the effects of LLLT administered to adolescents with a diagnosis of TMD [1-3,6,7,11-13,20-25].

The aim of the proposed study is to assess the effect of LLLT on pain, occlusal contacts, mandibular movements, and electromyography activity in the masseter and temporal muscles in adolescents with TMD.

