#### Evaluation of mandibular range of motion

The guidelines of the International Association for Dental Research will be followed when evaluating the range of motion of the mandible; the guidelines recommend a single measurement of each movement [31]. The volunteer will be instructed to open the mouth as wide as possible. Maximum voluntary mouth opening (distance between upper and lower central incisors) will be recorded with the aid of a digital caliper. The volunteer will then be instructed to exert pressure on the lower teeth with the index and middle finger to obtain maximum passive mouth opening and move the mandible to the right and left for the determination of excursion (distance between upper and lower midpoints). These procedures will be carried out at the beginning and end of treatment as well as 30 days after the last session [1,2].

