#### Evaluation of pain

A visual analog scale will be used before and after LLLT as well as 30 days after the last session to record pain upon palpation of the masseter and temporal muscles [1,2,9,24]. This is a numeric rating scale that runs from 0 (absence of pain) to 10 (worst pain imaginable) [1].

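### Named comparative tests cover only EMG and occlusal contacts; pain and mandibular movement are reached only by a non-normal fallback, and the 30-day visit has no named analysis

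*Protocol article*

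**What the plan says.** The aim, at the end of the Background, is to "assess the effect of LLLT on pain, occlusal contacts, mandibular movements, and electromyography activity" in adolescents with TMD, which makes four outcomes.

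Three of them are scheduled at three times. For pain, the 0 to 10 rating "will be used before and after LLLT as well as 30 days after the last session to record pain upon palpation". For mandibular range of motion, "These procedures will be carried out at the beginning and end of treatment as well as 30 days after the last session". The section on occlusal contacts sets the same three times. EMG is scheduled before and after the laser course only (Surface electromyography).

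The section Organization and statistical treatment of data then sets out:

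- a paired t test "to analyze the averages of electromyographic and occlusal contacts before and after treatment";
- a between-group sentence, in which the t test and "analysis of variance will be used to compare mean electromyographic signals and occlusal contacts between different groups";
- a fallback: "For data that are not normally distributed, the differences before and after treatment in the same group and between groups will also be analyzed", by Mann–Whitney and Wilcoxon tests;
- general statements on descriptive statistics, chi-square and Fisher tests for categorical variables, and correlations: "Pearson’s correlation coefficients will be calculated for the analysis of correlations among the continuous variables".

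The abstract is narrower still. It ties the t test and analysis of variance to EMG signals alone.

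**The concern.** The analysis section does not speak of continuous outcomes in general. It picks two of the four by name and leaves two out, and it does not mention a visit that three of the outcome sections schedule. One of the omitted outcomes is pain, and the Discussion justifies the trial by pain relief and quality of life.

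If the section is followed literally, whether pain and mandibular movement get a between-group test depends on whether the data turn out non-normal. Pain and movement at 30 days get no laser-versus-placebo comparison on either branch. With four TMD groups and three visits, the comparison, time and test for these outcomes could then be chosen after the results are seen. Whether any benefit lasts, the evident purpose of the 30-day visit, would have no prespecified answer.

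**Working it through.** The article gives no numerical figure on this point; its only sample-size calculation rests on masseter EMG and does not enter here. The check sets the outcome sections beside the statistics section.

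**Step 1. Match each outcome to its schedule and to the tests that name it.**

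| Outcome | Before | End | 30 days | Named in paired t test | Named in between-group t test/ANOVA | Non-normal clause |
|---|---|---|---|---|---|---|
| Pain | yes | yes | yes | no | no | before/after difference, if non-normal |
| Mandibular movement | yes | yes | yes | no | no | before/after difference, if non-normal |
| Occlusal contacts | yes | yes | yes | yes (before/after) | yes (no time given) | before/after difference, if non-normal |
| EMG | yes | yes | no | yes (before/after) | yes (no time given) | before/after difference, if non-normal |

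**Step 2. Count.** Outcomes in the aim: 4. Named in a paired or between-group test: 2 (EMG, occlusal contacts). Named in neither: 4 − 2 = 2 (pain, mandibular movement). Outcomes measured at 30 days: 3. Of these, with a test that names the 30-day visit: 0.

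**Step 3. Follow pain and movement through each branch.**

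- Data judged normal: no sentence assigns a treatment comparison.
- Data judged non-normal: the clause names no outcome, so it reaches them. It gives before/after differences, compared within and between groups.
- 30-day values: the clause speaks of before and after. The pain section lists the 30-day reading in addition to the before and after readings, so in the article's own usage the 30-day value is a separate time. Neither branch covers it.

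The remaining methods do not fill the gap. Pearson correlations are not a treatment comparison. Chi-square and Fisher tests apply to categorical variables, and neither pain on a 0 to 10 scale nor a caliper distance is one as measured.

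**Step 4. Size of the prespecified set once the gap is closed.** The laser groups are II, III and IV, and placebo is V, so there are 3 laser-versus-placebo contrasts. At two post-treatment times this is 3 × 2 = 6 per outcome. The range-of-motion section describes four measurements (voluntary opening, passive opening, right and left excursion), which gives 4 × 6 = 24 contrasts for movement alone. The fix therefore has to say which contrast and time lead.

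**The case against.** The strongest reply is that this is a condensed article. A test-by-test listing for every outcome and visit is often left to a full protocol or analysis plan, which is not shown. That has force for the 30-day visit taken alone, which is closer to ordinary omission. It does not dispose of the point, because the section names the outcomes to be tested and its list disagrees with the aim and the outcome sections of the same article. A general sentence about comparing continuous outcomes between groups would have raised no issue on outcome coverage.

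A reader might infer several stronger things that the article does not support:

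- *That all stated tests are before/after only.* The between-group sentence carries no such limit and gives no time. A 30-day comparison of occlusal contacts is unspecified, not excluded.
- *That pain and movement get no treatment comparison, or only descriptive results.* The non-normal clause is open to any outcome and includes between-group comparison. A 0 to 10 rating in groups of 17 may well fall under it. The coverage is conditional, not absent.
- *That the paired tests would be run pairwise over three visits, dropping participants with a missed visit.* The article proposes no such analysis.
- *That pain is the designated lead outcome.* The Background lists it first, but the abstract's aim lists it last, the sample size rests on EMG, and no outcome is designated primary.

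It is also fair to say that a mixed model is one option. Adding pain and movement to the existing between-group sentence, with time points, would close the naming gap.

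**Conclusion.** The point holds in a limited form. Two of the four stated aims have no named test and are reached only through an outcome-neutral fallback that depends on non-normality and covers before/after differences. None of the three outcomes measured at 30 days has an analysis that names that visit. This is a mismatch within the article, not merely detail left to another document.

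The conclusion assumes that the statistics section means what it lists, and that its before/after wording excludes the 30-day reading, as the outcome sections' own usage suggests. It does not show that pain and movement will go untested, or that 30-day comparisons are ruled out; it shows that the text does not commit to them. No bias or loss of power is quantified, and none is claimed. Under Trial status the study is still recruiting, so the wording can be settled before results are known.

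**What to change.** Extend the between-group analysis to pain and to each mandibular movement. For these and for occlusal contacts:

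- Analyse Groups II–V, the groups with TMD that receive laser or placebo. Group I has no TMD and receives no intervention, so it is not part of this comparison.
- Fit one repeated-measures model per outcome to the end-of-treatment and 30-day values, with terms for group, time, group-by-time and the baseline value. With two post-treatment times, an unstructured covariance needs only two variances and one covariance. Include every participant with at least one post-treatment value.
- Report each laser-versus-placebo difference with its 95% CI at each time.
- Name the main contrast and time, or label the rest of the six contrasts per outcome as secondary.
- State how the non-normal clause relates to this model, for example as a sensitivity analysis, so that the choice of test does not decide whether a comparison is made.

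The minimum alternative is to add pain and mandibular movement to the existing between-group sentence and to state the time points for every outcome. That closes the gap in naming, but does not give a single baseline-adjusted comparison across both visits.

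The cost is revised wording and modest extra analysis work. All the measurements are already scheduled, so no new visits, participants or data collection are needed.
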